#### Gut hormones and bile acid:

These will be measured in the fasted and/or postprandial state for each patient and compared within and between the groups using parametric/non-parametric repeated measures statistical testing. Regressions will be performed with clinical outcomes (i.e. BMI, glucose control) to identify predictive markers and generate mechanistic hypotheses.

#### Appetite food hedonics and brain reward systems:

Comparison of brain activation during fMRI paradigms and outcomes from behavioural measures of food hedonics and questionnaires will be compared between groups using a 2x2 ANOVA design including group (control vs. Endobarrier) between subject factor, time (baseline vs. follow-up visit) within subject factor, and group x time interaction to identify differential effects between groups. For fMRI studies analysis will use region of interest analyses (e.g. for food pictures orbitofrontal cortex (OFC), amygdala, caudate, nucleus accumbens and anterior insula; for MID task nucleus accumbens, dorsal striatum and OFC; for Go-NoGo task pre-supplementary motor area). In addition whole brain analysis will be performed to compare groups using statistical thresholds of voxel-wise correction FDR  $P < 0.05$  and cluster-wise correction  $Z > 2.3$   $P < 0.05$ . In addition linear regression will be performed to measure the correlation of variables at baseline or during the intervention with primary outcomes at 1 year e.g. weight loss and decreases in HbA1c within each group, to generate predictive markers and generate mechanistic hypotheses.

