## 3 STUDY DESCRIPTION

### 3.1 Design

This study is a randomised controlled trial of the EndoBarrier device compared with standard medical therapy for the management of obese subjects with T2DM. Subjects will be randomised to one of the two treatment arms (see Table 1) of the study via the InForm system (the eCRF database for the study). Over 24 months, the study will be performed at two investigational sites, Imperial College Healthcare NHS Trust in London and University Hospital Southampton NHS Foundation Trust.

Individuals in both study arms will be invited regular medical check-ups including measurement of weight, blood pressure, and blood parameters (HbA1c, cholesterol, triglycerides, fasting blood glucose, insulin), quality of life (EQ-5D) and use of health services, as well as to record any adverse events and medications. Diabetes medication titrations will be conducted by the study diabetologists/endocrinologists in accordance with the guidelines of the American Diabetes Association (see section 5.5.1 for full details). They will also receive routine dietary and exercise counselling as well as telephone counselling from a specialist dietitian. The control arm will be invited for routine follow-up visits to review their standard medical care. Both arms will also be invited to undergo a diversity of tests investigating the mechanism of the EndoBarrier. After 12 months, the EndoBarrier will be removed and both arms will be followed up for a remaining 12 months.

In order to investigate the mechanism of the effect of the EndoBarrier Device, the trial is divided into three sub-groups in each arm who will have the following additional assessments at visits 3, 5, 8 and 10, 14 (see section 5.4 and 5.6 for more detail):

- Sub-group 1 (minimum n=24): functional MRI, eating behaviour, cognitive assessment, and post-meal gut hormones
- Sub-group 2 (minimum n=18): insulin clamps

|                                                                                   |                                                                             |                                    |                                               |                                            |

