|-----------------------------------------------------------------------------------|-----------------------------------------------------------------------------|------------------------------------|-----------------------------------------------|--------------------------------------------|
| [figure not shown] | Title:
EndoBarrier TM
Gastrointestinal Liner
Diabetes Trial | Protocol No:
Version 5.0 | Sponsor:
Imperial College
London | Date:
5 th March 2018 |
|-----------------------------------------------------------------------------------|-----------------------------------------------------------------------------|------------------------------------|-----------------------------------------------|--------------------------------------------|

- Sub-group 3 (minimum n=18): assessment of taste and food preference, eating behaviour assessment, and post-meal gut hormones

Participation in the sub-groups is optional.

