### 5.6.8 Functional MRI (sub-group 1 only)

Twenty-four subjects in each group (Treatment and Control) will have fMRI scans to examine between brain function related to food reward and addictive behaviours at baseline and early after intervention, and these will be correlated psychological questionnaires and computerised tasks, and test meals.

The study visits will last up to 6-8 hours (Visit 3 and 8), and 3 hours (Visits 5, 10 and 14). Subjects will attend the NIHR/Wellcome Imperial Clinical Research Facility and Clinical Imaging Facility at the Hammersmith Hospital in the morning or at lunchtime.

The paradigms and psychological/cognitive tests used in the fMRI protocol have already been approved in a study looking at the longitudinal effects of dietary interventions, bariatric surgery and

|                                                                                   |                                                                                                  |                                           |                                                             |                                                  |
|-----------------------------------------------------------------------------------|--------------------------------------------------------------------------------------------------|-------------------------------------------|-------------------------------------------------------------|--------------------------------------------------|
| [figure not shown] | Title:
EndoBarrier TM
Gastrointestinal Liner
Diabetes Trial | Protocol No:
Version 5.0 | Sponsor:
Imperial College
London | Date:
5th March 2018 |
|-----------------------------------------------------------------------------------|--------------------------------------------------------------------------------------------------|-------------------------------------------|-------------------------------------------------------------|--------------------------------------------------|

drugs in obesity (10/H0707/60, Functional magnetic resonance of brain food reward in obesity and its treatment).

Subjects will be advised to avoid alcohol and strenuous exercise the day before and day of each study visit, and will be asked to fast from the evening before the visit if a morning scan/visit, or from breakfast for an afternoon scan/visit.

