#### Insulin Clamps:

Overall and tissue specific insulin sensitivity will be quantified for each patient and compared within and between the groups at 3 time points using parametric/non-parametric repeated measures statistical testing. Regressions will be performed with clinical outcomes (i.e. BMI, glucose control) to identify predictive markers and generate mechanistic hypotheses.

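### The 2x2 group-by-time ANOVA for fMRI, food-hedonic and questionnaire outcomes is a change-score test; adjusting for the Visit 3 baseline would be more precise, by an amount that depends on a correlation the protocol does not give

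*Protocol*

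**What the plan says.** In Section 8.2, the paragraph on appetite, food hedonics and brain reward states that these outcomes are "compared between groups using a 2x2 ANOVA design including group (control vs. Endobarrier) between subject factor, time (baseline vs. follow-up visit) within subject factor". The treatment effect is carried by one further term of the same model, which the paragraph gives as "and group x time interaction to identify differential effects between groups". No baseline covariate is named.

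The numbers behind these outcomes differ:
- **fMRI:** Section 5.6.8 says "Twenty-four subjects in each group (Treatment and Control) will have fMRI scans", with one scan before treatment (Visit 3) and one after (Visit 8).
- **Computerised eating-behaviour tasks:** done by sub-groups 1 and 3 (Section 5.6.5).
- **Eating and behaviour questionnaires:** completed by sub-groups 1 to 3 (Section 5.6.1).

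Section 3.1 sets the minimum sizes for each arm. The imaging entry reads "Sub-group 1 (minimum n=24): functional MRI, eating behaviour, cognitive assessment, and post-meal gut hormones". The clamp entry, with a smaller minimum, reads "Sub-group 2 (minimum n=18): insulin clamps". The taste entry has that same smaller minimum and reads "Sub-group 3 (minimum n=18): assessment of taste and food preference, eating behaviour assessment, and post-meal gut hormones". The tasks and questionnaires are measured at Visits 3, 8, 10 and 14, so they have three follow-up visits where the 2x2 layout admits one, which is not named.

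Elsewhere in Section 8.2 adjustment is planned. The main logistic regression adjusts for BMI group and site, and the cost and QALY regression adjusts for baseline differences.

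**The concern.** Every sub-group patient has a Visit 3 measurement, and the only use the planned test makes of it is to subtract it. Subtraction gives the baseline a weight of one whatever its correlation with follow-up. If rho is below 0.5, the change score is noisier than the follow-up value alone. A covariate model estimates the weight from the data and, apart from one degree of freedom, cannot do worse in a randomised comparison.

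The protocol names the method in this paragraph, so the point concerns a stated choice and not detail left to an SAP. At stake is precision on mechanism, a listed secondary objective (Section 2.2), in small sub-groups where a null result is hard to interpret. Visits in the fMRI sub-group that include a scan last up to 6 to 8 hours, so discarded precision is costly there.

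**Working it through.** **The plan's own figure.** The only sample size backed by a power statement is for the primary endpoint: 35% v 15%, 80% power, two-sided 5%. n = [1.96 x sqrt(2 x 0.25 x 0.75) + 0.842 x sqrt(0.35 x 0.65 + 0.15 x 0.85)]^2 / 0.20^2 = 72.4, so 73 per group, as stated. It does not depend on the analysis discussed here. No power, SD, effect size or rho is given for the mechanistic outcomes.

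**Inputs.** Two-sided 5% (Section 8.2). Per arm: fMRI 24; tasks 24 + 18 = 42 at least; questionnaires 24 + 18 + 18 = 60 at least. Assumed, because not stated: rho from 0.3 to 0.9, effects from 0.5 to 0.8 SD, equal variance at both times.

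**Step 1: the planned test.** In a two-group, two-time ANOVA the interaction F equals the squared t on change scores. A numerical check with 24 per arm gave 1.355 for both.

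**Step 2: variances**, in units of the outcome variance:
- change score: 2(1 - rho)
- follow-up adjusted for baseline: 1 - rho^2
- ratio, adjusted to change: (1 + rho)/2, a saving of (1 - rho)/2

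The ratio is 0.65 at rho 0.3, 0.75 at 0.5, 0.85 at 0.7, 0.90 at 0.8 and 0.95 at 0.9. At rho 0.5 the planned test would need 24/0.75 = 32 per arm to match the precision of ANCOVA with 24.

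**Step 3: power, fMRI, 24 per arm.** Noncentral t with 46 df (change) and 45 df (ANCOVA). The ANCOVA variance is inflated by 1 + 1/(2n - 4) for estimating the slope. Each cell shows planned v ANCOVA.

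| rho | 0.5 SD | 0.6 SD | 0.8 SD |
|---|---|---|---|
| 0.3 | 30% v 42% | 41% v 56% | 63% v 80% |
| 0.5 | 40% v 49% | 53% v 64% | 77% v 87% |
| 0.7 | 59% v 65% | 75% v 80% | 94% v 96% |
| 0.8 | 77% v 80% | 90% v 92% | 99.0% v 99.4% |
| 0.9 | 96.6% v 97.0% | 99.5% v 99.6% | both about 100% |

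If the effect is instead set so that the planned test has 80% power, ANCOVA has 93%, 89%, 85%, 83% and 81% at rho 0.3, 0.5, 0.7, 0.8 and 0.9. If it is set so that ANCOVA has 80%, the planned test has 63%, 69%, 74%, 77% and 79%. Simulation agreed: 79.4% v 92.5% at rho 0.3, 80.7% v 89.7% at 0.5 and 79.8% v 85.3% at 0.7.

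Leaving out the small-sample inflation adds about 1 point or less to each gain. That produces the upper ends of 18, 7 and 4 points at rho 0.3, 0.7 and 0.8; at rho 0.5 and 0.6 SD it would give 12 in place of 11.

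**Step 4: the larger outcome families, rho 0.5.**

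| Outcome | n per arm | 0.5 SD | 0.8 SD |
|---|---|---|---|
| Computerised tasks | 42 | 62.0% v 73.8% | 95.2% v 98.6% |
| Questionnaires | 60 | 77.5% v 87.8% | 99.1% v 99.9% |

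**Step 5: chance imbalance.** At 24 per arm the baseline difference has standard error sqrt(2/24) = 0.29 SD. An imbalance D moves the change-score estimate by (1 - rho)D in the opposite direction, so by 0.5 x 0.29 = 0.14 SD at rho 0.5 for a one-standard-error imbalance. This is the loss in Step 2 seen from another side, not an additional bias.

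**The case against.** The strongest case against is that the planned test is valid and unbiased under randomisation, that the protocol claims no power for these outcomes, and that none of them is a listed endpoint in Sections 2.4 and 2.5. A group-by-time layout also shows within-group change, which suits the stated interest in scanning the same patients before and after insertion. All of that stands. It limits the importance of the point, but it is no reason to keep the less precise between-group test, since within-group change can still be reported descriptively.

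A second objection is that Visit 3 is not a clean pre-allocation baseline. Patients learn their arm at Visit 2, and arm-specific dietary information is given then (Sections 5.2 and 5.5.3). Subjective scores could already differ by arm at Visit 3. This stands as a caveat, but it does not favour change scores: if disclosure shifts the baseline by d, the change score subtracts all of d and ANCOVA only rho x d.

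Three stronger readings are tempting and are not supported:
- **A loss of about ten points across all these outcomes.** 24 per arm applies to fMRI only, and the figure needs rho near 0.5, which the protocol does not give.
- **The same error in the other mechanistic analyses.** Gut hormones and bile acids are "compared within and between the groups using parametric/non-parametric repeated measures statistical testing" and clamp measures are "compared within and between the groups at 3 time points using parametric/non-parametric repeated measures statistical testing"; food preference is worded in the same way. These paragraphs fix no model, and a repeated-measures model with a baseline covariate is compatible with them.
- **The sub-groups as the only evidence on mechanism.** Table 2 schedules metabolomics, bioelectrical impedance and DNA/RNA sampling in all patients.

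**Conclusion.** The point holds as a loss of precision in a stated method. The interaction test in the appetite and brain-reward paragraph is a change-score test, and adjusting for Visit 3 would reduce the variance by (1 - rho)/2. For fMRI at 24 per arm the gain is about 9 to 11 power points at rho 0.5, 13 to 18 at 0.3, 3 to 7 at 0.7 and 0 to 4 at 0.8 to 0.9. For the tasks and questionnaires at rho 0.5 it is about 10 to 12 points for a 0.5 SD effect and 1 to 4 points for 0.8 SD.

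These figures rest on assumed correlations and effects, equal variances at the two times, and the minimum sub-group sizes. If the outcomes prove highly repeatable, little is lost. A reader might infer that the planned comparison is biased, or that the main result is at risk; neither follows. The test is valid, and the primary endpoint and its sample size are untouched.

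**What to change.** In the appetite and brain-reward paragraph of Section 8.2, replace the between-group interaction test for region-of-interest signals, behavioural measures and questionnaire scores with ANCOVA: follow-up value on group, Visit 3 value and BMI stratum, plus site where both sites contribute. Where there are several follow-up visits (tasks and questionnaires), use a repeated-measures model with the Visit 3 value as covariate.

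Whole-brain maps and descriptive within-group change may stay as they are. State as a caveat that Visit 3 follows disclosure of allocation at Visit 2, which matters most for subjective measures. The same approach may be adopted for the hormone, clamp and food-preference outcomes, whose current wording already allows it.

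The cost is a change of analysis wording. No visits, patients or data are added.

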### 2.2 Secondary objectives

- To compare the EndoBarrier with conventional medical therapy, diet and exercise for obesity related type II diabetes and their effectiveness on:
  - Metabolic state as defined by the International Diabetes Federation (IDF) with an HbA1c < 6% ( or < 42 mmol/mol)
  - Blood pressure < 135/85
  - Absolute weight loss
- To investigate the mechanism of the effect of the EndoBarrier via changes in:
  - Gut hormones
  - Microbiome
  - Appetite, food hedonics and brain reward systems
  - Body fat content
  - Food preference
  - Hepatic or peripheral insulin sensitivity
  - Bile acids
  - Biomarkers such as genetic markers
- To estimate the cost-effectiveness of the EndoBarrier device compared with conventional treatment over the trial period (within trial analysis).
- To estimate the long-term cost-effectiveness (over 24 months) of the EndoBarrier device compared with conventional treatment and alternative surgical interventions.

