### 5.5.13 DNA and RNA sampling

Blood (15 ml) will be taken at visit 3, 5, 8, 10 and 14 with specific consent to extract DNA and RNA for examination of genetic markers which predict weight loss, genetic abnormalities causing or contributing to obesity and insulin resistance (including array comparative genomic hybridization for copy number variations, epigenetic analysis, whole genome or exome sequencing, DNA sequencing of candidate genes (such as MC4R, POMC, leptin receptor, SIM1); and polymorphisms or mutations associated with obesity, diabetes mellitus, PCOS, fat distribution and body composition (using PCR based SNP analysis). RNA will be extracted from blood to perform genome-wide expression analysis.

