## 8.2 Data Analysis

Patient characteristics will be summarized. Summaries of continuous variables will be presented as means and standard deviations if normally distributed, and as medians and inter-quartile ranges for skewed data, whilst categorical variables will be presented as frequencies and percentages. The difference between the two study groups in the proportion of patients achieving substantial improvement in the metabolic syndrome both at 12 and 18 months will be analysed using logistic regression adjusting for the stratification variables (BMI groups and sites). Analysis of secondary outcomes will be conducted using standard statistical procedures applicable to categorical or continuous data as appropriate. For missing values we will explore the pattern and the extent of missingness and we will carry out an appropriate form of multiple imputation if required. The analysis will be performed according to the intention to treat principle. All statistical tests will be two-tailed with a 5% significance level.

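### Section 8.2 looks for predictive markers by regression within each arm, which cannot separate prognosis from response to the device; one pooled marker-by-arm model would be a cheap exploratory improvement

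*Protocol*

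**What the plan says.** Section 2.2 gives the purpose of the mechanistic work: "To investigate the mechanism of the effect of the EndoBarrier via changes in". The list that follows covers gut hormones, food hedonics, insulin sensitivity and other measures.

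The paragraph of section 8.2 on appetite, food hedonics and brain reward has two parts:

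- A 2x2 ANOVA on the fMRI, behavioural and questionnaire measures, with arm, time "and group x time interaction to identify differential effects between groups".
- A marker analysis, whose method is stated as "linear regression will be performed to measure the correlation of variables at baseline or during the intervention with primary outcomes at 1 year e.g". The sentence then names the example outcomes, the arm-by-arm fitting and the aim: "weight loss and decreases in HbA1c within each group, to generate predictive markers and generate mechanistic hypotheses". No marker-by-arm term and no baseline covariate are stated.

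The paragraphs on gut hormones and bile acid, food preference and insulin clamps share another sentence: "Regressions will be performed with clinical outcomes (i.e. BMI, glucose control) to identify predictive markers and generate mechanistic hypotheses". They do not say whether these regressions are fitted per arm or pooled.

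Section 5.6.8 gives the size of the fMRI sub-group: "Twenty-four subjects in each group (Treatment and Control) will have fMRI scans". Section 3.1 sets a minimum of 18 for each of sub-groups 2 and 3. The general rule in section 8.2 is "All statistical tests will be two-tailed with a 5% significance level".

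**The concern.** The effect of the device is a difference between arms. A marker informs on who responds to the device only if that difference changes with the marker. The regression within an arm tests something else, namely whether the marker goes with the outcome under that arm's treatment. A purely prognostic marker, with the same slope in both arms, gives a real association there and yet says nothing about the device. Finding significance in the device arm and not in the control arm does not help, because a difference in significance is not a test of a difference in slopes.

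The interaction already in the paragraph does not fill the gap. Group by time asks whether the brain, behavioural and questionnaire measures change differently between arms. It does not ask whether such a measure modifies the device's effect on HbA1c or weight.

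A second, smaller issue is that the outcome is a decrease in HbA1c. It contains the baseline value, so a marker related to baseline HbA1c will tend to correlate with the decrease through regression to the mean alone.

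At stake is how a set of exploratory findings is read. Both arms provide the markers, so the data to separate prognosis from response are already planned.

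**Working it through.** **Figures in the plan.** The protocol gives no sample size, correlation or power for the marker regressions, so there is no figure to reproduce. Its main-trial size (73 per group for 35% versus 15%, 80% power) does reproduce, with computed power of 80.3%, and is not in question here.

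**Inputs.**

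- 24 per arm for fMRI, from section 5.6.8. 18 per arm is also run, taking the sub-group 2 and 3 minimum in section 3.1 as per arm.
- Two-sided 5%, from section 8.2.
- All correlations are assumptions, because the protocol states none.

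**1. Prognostic marker, same correlation r in both arms.** Simulation (40,000 trials) compared the slope test in each arm with the pooled test of slope difference. Results at 24 per arm:

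| r in both arms | device arm significant | at least one arm | device arm only | marker-by-arm test |
|---|---|---|---|---|
| 0 | 4.9% | 9.6% | 4.7% | 4.9% |
| 0.3 | 30% | 51% | 21% | 4.9% |
| 0.5 | 73% | 93% | 20% | 5.1% |
| 0.6 | 90% | 99% | 9% | 4.8% |

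Hand check by Fisher's transformation: power is about Φ(atanh(r)·√(n−3) − 1.96).

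- r = 0.3: 0.3095 × √21 = 1.418, and Φ(−0.542) = 0.29.
- r = 0.5: 0.5493 × √21 = 2.517, and Φ(0.557) = 0.71.

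The device-arm-only column is also as expected from two independent arms: 0.30 × 0.70 = 0.21 and 0.73 × 0.27 = 0.20.

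**2. Coupling with baseline.** Let B and F be HbA1c at baseline and one year, with unit variance and correlation ρ. The marker correlates 0.6 with B and has no other link to F. Then

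corr(marker, B − F) = 0.6(1 − ρ) / √(2(1 − ρ)) = 0.6·√((1 − ρ)/2).

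- ρ = 0.5: 0.6 × √0.25 = 0.30, and the within-arm test is significant in about 30% of trials at 24 per arm.
- ρ = 0.7: 0.6 × √0.15 = 0.23, and it is significant in about 19%.

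With the baseline value of HbA1c in the model, the same simulation returns to about 5% in both cases.

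**3. Power of the marker-by-arm test.** Take a true correlation of 0.5 in the device arm and 0 in control. Simulated power is 40% at 24 per arm and 31% at 18 per arm. Hand check: 0.5493 / √(2/21) = 1.78, and Φ(−0.18) = 0.43; 0.5493 / √(2/15) = 1.50, and Φ(−0.46) = 0.32.

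**The case against.** The other side has a good deal in its favour.

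- **Predictive may mean prognostic.** Section 5.5.13 speaks of blood taken "for examination of genetic markers which predict weight loss", which is prediction of an outcome, and the marker sentence in section 8.2 speaks of correlation with outcomes. On that reading, the 30% and 73% above are valid power and not false positives. This stands. The protocol does not define the word, and the stronger reading rests on the mechanism objective.
- **No marker is declared anything.** A reader might infer that any marker associated with outcome in both arms will be announced as predicting the device's effect, or used to select patients. The protocol does not support this. It has no declaration rule, lists no marker among its endpoints, proposes no marker-based selection, and describes the work as hypothesis-generating.
- **The randomised comparison is not discarded.** The mechanistic measures are compared between arms, through the group-by-time term or repeated-measures tests. This stands. What is missing is narrower: no between-arm contrast is stated for the link from marker to clinical outcome.
- **Only one paragraph says the regressions are per arm.** The gut hormone, food preference and clamp paragraphs leave the model form open. A protocol may leave that to the statistical analysis plan, which is not available here, so it is not an error.
- **Coupling may be weak for these markers.** The 0.6 correlation with baseline HbA1c has no source in the protocol, and it may be too high for brain activation or questionnaire scores.
- **The better test is weak.** At about 40% power it will settle little. That is a reason to report an interval. It does not make within-arm slopes informative about response.

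**Conclusion.** The point holds as a low-severity improvement to an exploratory analysis. The protocol fixes a per-arm method in one paragraph of section 8.2, and that method cannot by itself distinguish prognosis from response to the device. If the markers are meant to serve the mechanism objective, an equally prognostic marker would appear significant in the device arm in about 30% (r = 0.3) or 73% (r = 0.5) of trials at 24 per arm, against about 5% for a marker-by-arm test. Coupling with baseline HbA1c adds a separate route to significance, about 19% to 30% under a marker-baseline correlation of 0.6 and a baseline-to-one-year correlation of 0.7 to 0.5.

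These sizes rest on assumed correlations, normal data and equal variances. They count as error only for statements about response to the EndoBarrier; for a purely prognostic question, the equal-slope figures are ordinary power. Primary endpoint conclusions do not depend on this.

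**What to change.** In the appetite and brain-reward paragraph of section 8.2, or in the statistical analysis plan:

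1. For each baseline marker, add one pooled model of the one-year outcome on arm, marker, marker-by-arm and the baseline value of that outcome.
2. Report the interaction estimate with its interval as exploratory, and base any statement about response to the EndoBarrier on it.
3. Keep the within-arm slopes, labelled as prognostic associations.
4. Report markers measured during the intervention as descriptive. They are post-randomisation and may be mediators, so an interaction term does not settle their role.
5. Use the same model for the regressions in the gut hormone, food preference and insulin clamp paragraphs, where the arm structure is not stated.

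The cost is a few sentences and one extra model per marker on data already planned in both arms. The downside is the low power given above for the interaction (about 40% at 24 per arm and 31% at 18), so fewer markers will be flagged.
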